### Data collection

Outcomes and other measures will be assessed with patient questionnaires based on reliable, valid, and responsive instruments (see Table 2). Baseline questionnaires and a return envelope addressed to the University of Lübeck will be handed to the participants during the initial consultation by the trained occupational health physicians. Patient questionnaires for the six-month follow-up will be sent by mail to the participants six months after random assignment by the three rehabilitation centers with a return envelope addressed to the University of Lübeck. The questionnaires at the end of the two-day diagnostics will handed out to the participants by the study coordinators in the rehabilitation centers together with a return envelope addressed to the University of Lübeck. The patient forms and questionnaires have been tested in a previous pilot study.

The occupational health physicians will be trained for the required computerized documentation before the randomized controlled trial begins. The occupational health physicians will send the computerized documentation of the initial and follow-up consultations quarterly to the researchers, who will check it for completeness and validity.

The study coordinators will document the two-day comprehensive diagnostics and send the pseudonymized computerized documentation to the researchers after completion of the diagnostics.

If participants withdraw their consent, the collected data will be deleted. A single reminder will be sent three weeks after the first mailing of the six-month follow-up questionnaires, again containing the questionnaire and the return envelope addressed to the researchers.

We have created a website to inform study participants about the study, and to maintain interest in the study.

Interviews will take place after the two-day diagnostics, during the process of the follow-up consultations.

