### Trial design

Our study is a randomized controlled trial with two parallel groups, comparing individuals in the intervention group with individuals in a waiting-list control group. Employees with health restrictions and limited work ability from the participating companies are randomly assigned to the intervention or waiting-list control group. The intervention consists of a comprehensive diagnostic service, initiated and followed-up by occupational health physicians. The waiting-list control group will receive the intervention six months after study inclusion. A similar approach was adopted in a randomized controlled trial analyzing the effectiveness of pulmonary rehabilitation in patients with asthma [17]. The use of a waiting-list control group allows all eligible individuals to participate in the intervention. We expect that this will support willingness to participate in our randomized controlled trial and eliminate potential reservations about randomized assignment among both participating companies and potential study participants.

Questionnaire data was used to analyze the effects of our intervention, and assessed at study inclusion (initial consultation) and six months later in both groups. We will also assess the therapy dose received and delivered at the end of the two-day comprehensive diagnostics. Individual interviews with participants supplement our study with qualitative data.

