#### Control

The control group will receive the comprehensive two-day diagnostics and subsequent follow-up consultations with the occupational health physician six months after the initial occupational health consultation.

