### Allocation

A separate randomization sequence will be created by the principal investigator (MB) for each rehabilitation center using Stata 16.0. Blocks of four and six will be combined in the computer-generated randomization lists, in order to guarantee balanced case numbers, even if the lists cannot be processed completely. The randomization envelopes are consecutively numbered and non-transparently sealed.

Participants will be informed that there are two different study groups (intervention and control group), and that allocation to the two groups is randomized, during the initial consultation with the occupational health physician. After a participant has given their consent, the occupational health physician will contact the study coordinator and register them for the two-day diagnostics. The study coordinator will then open the randomization letter and communicate the group assignment to the occupational health physician and the participant by telephone, and coordinate the start of the two-day diagnostics.

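### On the stated dates, the control arm's six-month questionnaire is posted on or after the day its own diagnostics are due, so some control Work Ability Scores can be recorded after the intervention has begun

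*Protocol article*

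**What the plan says.** Four places in the protocol article set the timing.

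- **Control:** the waiting-list arm gets its diagnostics and "follow-up consultations with the occupational health physician six months after the initial occupational health consultation". Trial design says the same from a differently named starting point: "The waiting-list control group will receive the intervention six months after study inclusion". That section also identifies study inclusion with the initial consultation, so these two agree.
- **Data collection:** the follow-up questionnaire "will be sent by mail to the participants six months after random assignment", in both arms, from the rehabilitation centers. For those who do not reply, "A single reminder will be sent three weeks after the first mailing of the six-month follow-up questionnaires", and the form is enclosed again.
- **Allocation:** randomization comes after consent at the initial consultation. "After a participant has given their consent, the occupational health physician will contact the study coordinator and register them for the two-day diagnostics". Then "The study coordinator will then open the randomization letter and communicate the group assignment".
- **Table 3:** the follow-up questionnaire has its own column, dated six months after the initial consultation, and that column stands before the one for control diagnostics.

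Statistical methods provides multiple imputation for incomplete follow-up responses.

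**The concern.** The objective compares the intervention with controls who have not yet started it. The control WAS therefore has to be taken before that arm's diagnostics. WAS asks about current work ability, so a form filled in late describes the participant after diagnostics and not at the end of the waiting period.

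Only the control arm is exposed to this error, so randomization does not cancel it. The planned imputation does not remove it either: a late control form is complete, would be analyzed as an untreated outcome, and could also inform the imputed values of control participants who did not reply.

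If diagnostics help, the difference between arms is diluted. The direction is not guaranteed, because confrontation with one's own functional limits could also lower a self-rated score.

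**Working it through.** **Step 1. Dates.** Let C be the date of the initial consultation and R the date of randomization. Allocation places R after consent at the consultation, so R − C ≥ 0.

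- Control diagnostics due: C + 6 months (Control).
- First mailing: R + 6 months (Data collection).
- First mailing minus due date = (R + 6 months) − (C + 6 months) = R − C ≥ 0 days.
- Reminder minus due date = (R − C) + 21 days ≥ 21 days.

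Postal and completion time come on top. The article gives no value for R − C, and it may be zero. Even at zero, the first form leaves on the day diagnostics are due and the reminder three weeks after it.

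**Step 2. Comparison with Table 3.** The table wants the questionnaire first and dates it from C, not R. It therefore differs from Data collection in its anchor, and its column order says nothing about the reminder.

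**Step 3. The plan's own sample size.** Inputs from the Sample size section: difference 1 point, SD 2, two-sided 5%, power 80%. A two-sample t-test needs 63.8, so 64 per arm (128 in total), with power 80.1%. The stated 128 is reproduced. With 60% response, 210 × 0.6 = 126, or 63 per arm, and power is 79.5%.

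**Step 4. Illustration of dilution.** The article gives neither of the two inputs, so both are assumptions: share of control answers that are late, c = 10-40%; mean gain in WAS by then, g = 0.25-0.5 points.

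Diluted difference = 1 − c × g. Power is from an unadjusted two-sample t-test with SD 2 and 63 per arm.

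| c | g | Difference | Power |
|---|---|---|---|
| 0 | – | 1.00 | 79.5% |
| 10% | 0.25 | 1 − 0.025 = 0.975 | 77.5% |
| 10% | 0.5 | 1 − 0.05 = 0.95 | 75.3% |
| 30% | 0.5 | 1 − 0.15 = 0.85 | 65.8% |
| 40% | 0.5 | 1 − 0.20 = 0.80 | 60.6% |

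**Step 5. Effect of baseline adjustment.** Statistical methods includes the baseline score as a covariate. With an assumed correlation r between baseline and six-month WAS, the residual SD is 2 × √(1 − r²).

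- r = 0.3: SD 1.91; power 83% at 1.00 and 65% at 0.80.
- r = 0.6: SD 1.60; power 94% at 1.00 and 80% at 0.80.

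The absolute power in Step 4 is therefore pessimistic. The dilution of the difference itself is unchanged by adjustment.

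**The case against.** The strongest reply is that Table 3 already states the intended order, and that six months is a nominal interval and not a calendar day. Control diagnostics have to be arranged by the study coordinator, whose center also posts the questionnaire. The Objectives could be read as controls starting six months later than the intervention arm, which itself starts only shortly after the consultation. On that reading diagnostics fall after the nominal questionnaire date, and few forms, perhaps none, would be late. This stands as evidence of intent and as a reason not to assume a large late share. It does not settle the matter: the dated statements in Control and Data collection say otherwise, and nothing in the article ties the reminder to the diagnostics date.

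Three further points on this side stand.

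- A reader might count three competing starting points: study inclusion, initial consultation and randomization. Trial design equates the first two, so there are two.
- Response windows and the handling of late forms are commonly left to the full protocol or analysis plan, which are not shown. Their absence is no fault here; the conflict between stated dates is.
- The late share and early gain are assumed. The target effect reflects diagnostics plus up to four consultations over five months, so crediting half of it to a late control form is generous.

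A stronger remedy may also suggest itself: mailing both arms several weeks early and setting every late control form to missing in the primary analysis. An earlier reading could cut into the intervention arm's consultation period, and since recruitment is under way it would mix assessment times. Setting late forms to missing is a choice of estimand. Neither is needed to resolve the conflict.

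**Conclusion.** The point holds as a conflict of stated dates that reaches the primary outcome. Taken literally, the control form is posted zero or more days after control diagnostics are due, and the reminder at least 21 days after. Some control WAS values can therefore be post-diagnostic, contrary to the order in Table 3.

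A reader might infer that the control arm will in fact be contaminated, or that power will drop to about 60%. The documents support neither. The lag, the actual scheduling of diagnostics and the number of late forms are unknown. The 60.6% joins the most pessimistic assumed inputs to an unadjusted test that is not the planned analysis. The range 0.975-0.80 for the diluted difference shows only what would follow if the assumptions held. Dilution is the likelier direction, but it is not certain.

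Severity: should be fixed.

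**What to change.** 1. Reconcile the Control section, Table 3 and Data collection on one anchor for the questionnaire in both arms, namely the initial consultation. The intervention schedule stays with the trial team.
2. A common anchor alone leaves the first mailing on the due day and the reminder after it. So also state that the control arm's six-month WAS is to be completed before that participant's first diagnostic day. The coordinator, whose center posts the form and arranges the diagnostics, checks this and obtains any outstanding form beforehand.
3. Have respondents date the form.
4. Report by arm the number of forms completed after the date of step 2, with a sensitivity analysis that excludes or imputes late control values.

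The cost is a few lines of wording, a date field and a small coordination task. Completed forms go to the university and not to the center, so the coordinator needs confirmation of return. Assessment timing will vary slightly. The extra chasing falls on the control arm, so response rates should be shown by arm. Recruitment is ongoing, so mailings still to come can follow the corrected rule.

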### Data management

A comprehensive data protection concept has been developed with the data protection officer from German Pension Insurance North which clarifies the data processing, the rights of participants, and technical and organizational measures in order to ensure the secure and confidential collection, processing, and storage of data. Data from the questionnaires will be entered, reviewed and exported to statistical software packages for further analysis. Data input and data verification will be performed by trained research assistants.

Recordings from the interviews will be transcribed by trained assistants at the University of Lübeck. Names and places will be removed during the transcription process.

Access to the data is limited to the first and last author and research assistants on the research team, and data management is performed by these authors.

### Statistical methods

Linear mixed models will be used for continuous outcomes and logistic mixed models for binary outcomes. We will include a random intercept to consider varying outcomes in different rehabilitation centers.

Baseline scores of outcomes will be included as covariates. In order to perform an intention-to-treat analysis, we will use multiple imputation to augment incomplete responses to the six-month follow-up questionnaires. Exploratory moderator analyses examine whether estimates differ for sex, job position, size of company, and the rehabilitation center [36].

We will not perform interim analyses or specify a stopping rule. Statistical tests will be regarded as significant if the two-sided *p*-value is less than 0.05. An up-to-date version of Stata (StataCorp, College Station, Texas, USA) will be used to conduct analyses.

The interviews will be transcribed and analyzed using qualitative content analysis.

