#### Primary outcome

Our primary outcome is self-rated work ability using the single-item Work Ability Score (WAS), which is the first item of the Work Ability Index (WAI) and measures current compared with lifetime best work ability [20, 21]. The score ranges from 0 (completely unable to work) to 10 (work ability at its best). Higher scores indicate better self-rated work ability. The WAS is closely correlated with the entire Work Ability Index score [21], and predicts work disability and health-related early retirement [33–35]. The WAS is assessed during the initial consultation with the occupational health physician, and at the six-month follow-up, and also at the end of the two-day diagnostics.

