#### Other measures

Data for other variables will be collected at baseline in order to provide a description of the study sample at the end of the two-day diagnostics, to obtain the received therapy dose, and at the six-month follow-up to obtain an overall rating of interventions elements and information on healthcare utilization during the intervention and waiting period (Table 2).

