##### Work Ability Index

Work ability is assessed using the German version of the WAI questionnaire [20, 21]. The total WAI score ranges from 7 to 49 points. Higher scores indicate better work ability. Levels of work ability can be categorized as poor (7–27 points), moderate (28–36 points), good (37–43 points), and excellent (44–49 points).

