### Sample size

A total number of cases of 128 persons, (64 persons per intervention arm) is necessary (two-sided type I error rate: 5%, power: 80%) in order to ensure a difference of 1 point on the Work Ability Score (standard deviation = 2). The standard deviation was estimated according to comparable studies [21, 33–35]. Although we will use multiple imputations to perform an intention-to-treat analysis, we will increase the sample size to compensate for the potential loss of participants during our follow-up assessments. This ensures sufficient power even if only complete cases are analyzed. Assuming a response rate of 60% after six months, we will recruit 210 patients in total: 105 patients per group.

Of the 210 persons recruited, 18 participants (nine from each of the intervention and control group) will be recruited to take part in interviews.

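### Optional improvement: baseline Work Ability Index and sick-leave weeks, both already collected, could be prespecified as extra covariates in the primary Work Ability Score model

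*Protocol article*

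**What the plan says.** The Statistical methods section plans linear mixed models for continuous outcomes with a random intercept for rehabilitation centre. On covariates it says only: "Baseline scores of outcomes will be included as covariates". It plans multiple imputation of incomplete six-month questionnaires and does not list the variables in the imputation model.

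The Primary outcome section makes the WAS a single 0-to-10 item, the first item of the WAI, and calls it closely correlated with the WAI total. It gives no coefficient. Table 2 places the full WAI (7 to 49 points) under other measures, at baseline only. The introduction to that group gives its baseline purpose: "Data for other variables will be collected at baseline in order to provide a description of the study sample". Sick-leave duration in weeks is listed in Table 2 as a secondary outcome, measured at baseline and six months.

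On numbers, the Sample size section says: "A total number of cases of 128 persons, (64 persons per intervention arm) is necessary", for a 1-point difference with a standard deviation of 2. It then allows for loss: "Assuming a response rate of 60% after six months, we will recruit 210 patients in total: 105 patients per group".

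**The concern.** A single item is a noisy measure of work ability. The WAI total covers the same construct with more items and is collected at the same visit. Sick leave is prominent in the eligibility criteria and is likely to be prognostic. If either variable predicts the six-month WAS beyond baseline WAS, leaving it out of the primary model makes the confidence interval wider than the collected data require.

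There is a second, weaker strand. Follow-up is by mailed questionnaire with one reminder, nobody is blinded after allocation, and controls are still waiting for the service. Response could therefore depend on severity, and differently by arm. Missing at random is somewhat easier to believe when the analysis conditions on sick leave as well as on one self-rated item.

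What is at stake is a modest amount of precision and some robustness, not the validity of the primary test.

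**Working it through.** **The plan's own figures.** With a difference of 1, SD 2, two-sided 5% and 80% power, the normal approximation gives 63 per arm (126). The two-sample t-test gives 64 per arm (128, power 80.1%), as stated. At 60% response, 126/0.6 = 210 and 128/0.6 = 213.3. Recruiting 210 yields 210 × 0.6 = 126 completers, 63 per arm, with 79.5% power by t-test and no covariate. The stated figures reproduce, and they take no credit for baseline adjustment.

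**Assumed inputs.** None of these is in the protocol.
- r1, baseline WAS with six-month WAS: 0.5.
- r2, baseline WAI with six-month WAS: 0.45 to 0.60.
- c, baseline WAS with baseline WAI: 0.7 to 0.9, reflecting the close correlation described.

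**Baseline WAS only.** R² = 0.5² = 0.25, so the residual SD is 2 × √0.75 = 1.73. Power at 63 per arm is 89.5% (t) or 90.0% (normal).

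**Adding the WAI.** R² = (r1² + r2² − 2·r1·r2·c)/(1 − c²), and the cut in residual variance is 1 − (1 − R²)/0.75. For r2 = 0.50 and c = 0.8, R² = (0.25 + 0.25 − 0.40)/0.36 = 0.278 and the cut is 1 − 0.722/0.75 = 3.7%.

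| r2 | c = 0.7 | c = 0.8 | c = 0.9 |
|---|---|---|---|
| 0.45 | 2.6% | 0.9% | 0.0% |
| 0.50 | 5.9% | 3.7% | 1.8% |
| 0.55 | 10.5% | 8.3% | 7.0% |
| 0.60 | 16.3% | 14.8% | 15.8% |

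At c = 0.8 the gain in completers is 126 × [0.75/(1 − R²) − 1], or about 1, 5, 11 and 22 down the column. At r2 = r1·c = 0.40 it is exactly zero. When the WAI predicts only as well as the WAS (r2 = 0.50), the standard error falls by 0.9% to 3.0%.

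**Adding sick-leave weeks as well.** Assume r = −0.40 with the outcome, −0.35 with WAS and −0.45 with WAI, keeping r2 = 0.55 and c = 0.8.
- Regressing sick leave on WAS and WAI gives coefficients 0.028 and −0.472, and R² = 0.203.
- The covariance of its residual with the outcome is −0.40 − (0.028 × 0.5 − 0.472 × 0.55) = −0.154.
- The increment in R² is 0.154²/0.797 = 0.030, so R² = 0.3125 + 0.030 = 0.342.
- The cut is 1 − 0.658/0.75 = 12%, and 126 × (0.75/0.658 − 1) is about 18 completers. Power at 63 per arm is 93.0%.

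Sick leave without the WAI gives R² = (0.25 + 0.16 − 2 × 0.5 × 0.40 × 0.35)/(1 − 0.35²) = 0.270/0.8775 = 0.308, a cut of 7.7%. This is sensitive to the assumption: at r = −0.30 it is 0.235/0.8775 = 0.268, a cut of 2.4%.

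**Bias illustration.** Suppose response is 60% in both arms and, in controls only, falls by 0.5 log-odds per SD of baseline sick leave.
- With response probability p, the mean of p(1 − p) is about 0.226. Mean sick leave among control responders then shifts by about −0.5 × 0.226/0.6 = −0.19 SD.
- After adjustment for WAS, the covariance of sick leave with the outcome is −0.40 + 0.35 × 0.5 = −0.225.
- This raises the control mean by about 2 × 0.225 × 0.19, a bias of −0.08 to −0.09 points.
- In simulation, adding the WAI alone leaves about −0.06, and adding sick leave removes the bias.

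**The case against.** The strongest case against is that the protocol is not wrong here. Adjusting for the baseline value of the outcome and for centre is standard, valid and prespecified. That stands.

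Three stronger readings are tempting, and the protocol does not support them.
- **Precision is lost because 40% of outcomes will be missing.** A covariate lowers residual variance whatever the response rate. If the same variables sit in both the analysis and the imputation model and only the outcome is missing, imputation recovers essentially nothing from non-responders, before or after the change. The expected loss is already covered by recruiting 210.
- **The analysis relies on response being random given one item.** The imputation variables are not listed, which an article commonly leaves to the analysis plan. Calling the other baseline data descriptive does not bar them from imputation. If sick leave is already there, most of the bias point is met.
- **The gain is material.** The WAS is part of the WAI and closely correlated with it, which points to a small increment. The upper figures need the WAI to predict later WAS clearly better than the WAS itself does.

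It can also be said that the plural in the covariate rule might admit the baseline of every outcome, sick leave included. Each outcome's own baseline is the more natural reading, but the wording does not rule out the other.

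The bias example is constructed: missingness depends only on the variable then added, and the result is under a tenth of the 1-point target. What survives is that two collected and plausibly prognostic variables are not named for the primary model.

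**Conclusion.** A minor, optional efficiency and robustness suggestion; there is no error or contradiction to correct. With baseline WAS to outcome at 0.5, the WAI alone cuts residual variance by 0% to about 15% (16% at the edge of the grid), and by 2% to 6% if it predicts only as well as the WAS. In the scenario with sick leave as well (WAI 0.55, sick leave −0.4), the cut is about 12% and power at 63 per arm goes from 89.5% to about 93%. Only the top of the assumed range (WAI 0.60) takes it to about 94%. All of this rests on assumed correlations.

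The planned 80% power needs none of it. Conditioning on sick leave also makes missing at random somewhat more plausible, by an amount that the protocol gives no basis to size.

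**What to change.** In Statistical methods, add one sentence naming baseline WAI total and baseline sick-leave weeks as fixed covariates in the primary WAS model, alongside baseline WAS and the centre intercept. State that both also enter the imputation model for the six-month WAS, if the analysis plan does not already say so.

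The cost is wording and two degrees of freedom, with no new data collection. The WAI is longer than the single item and will have some blanks; these baseline values must be imputed so that no participant drops out of the primary analysis. The change should be made before outcome data are examined, because the analysts will know group assignment and covariates chosen later would be open to challenge.
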